## Abstract

**Background:**

While quitting smoking dramatically decreases overall mortality, general practitioners (GPs) are less likely to prescribe medications for smoking cessation than other cardiovascular risk factors. Guidelines recommend providers first assess patients’ “readiness” to quit, an “opt-in” strategy, but only a minority of tobacco users are ready to quit on a given day. An “opt-out” strategy offering treatment as the default choice increased quit attempts in hospital and with pregnant women, but has not been tested in primary care. We will assess the efficacy of training GPs to offer treatment as the default choice using an encounter decision aid with current smokers seen in primary care.

**Methods:**

This is a pragmatic cluster-randomized controlled superiority trial with block randomization at the GP level in private practice in French-speaking Switzerland. GPs will be blinded to the arm allocation. The intervention is a half-day training course teaching an ‘opt-out’ approach to smoking cessation using an encounter decision aid (paper or electronic). GPs in the enhanced usual care group receives a brief refresher training about smoking cessation without changing their behaviour. GPs in both arms will recruit 23 patients each prior to routine primary care visits. The primary outcome is the effect of consulting a GP who received the intervention on the 7-day, point prevalence, smoking abstinence 6 months after the baseline appointment. Secondary outcomes include continuous abstinence; number of quit attempts; use of smoking cessation aids; patient-perceived involvement in discussions; and changes in GP behaviour. Patient outcomes will be collected using paper and telephone questionnaires. Assuming 15% drop-out, recruiting 46 GPs with 23 patients each will give us 80% power to detect an increase in smoking cessation from 4% (control) to 10.5% (intervention), with an alpha < 0.05.

**Discussion:**

GP visits are an opportunity to administer proven smoking cessation treatments. We hypothesize GPs offering smoking cessation treatment as the default choice using an encounter decision aid will increase the number of patients who quit. This study could significantly change our approach to smoking cessation in primary care. Default choices and the electronic decision aid are low-cost, easily diffusible interventions.

**Trial registration:**

ClinicalTrials.gov Identifier: NCT04868474, First Posted May 3, 2021, Last Update Posted October 6, 2021.

**Supplementary Information:**

The online version contains supplementary material available at 10.1186/s12875-022-01859-9.

## Background

In Switzerland, over a quarter of the population aged 15 years and older are current smokers. Smoking remains the most important cause of preventable death [1]. Smoking cessation significantly reduces all-cause mortality at all ages [2]. To help with smoking cessation, evidence-based smoking cessation guidelines recommend nicotine replacement therapy (NRT), bupropion and varenicline as first-line therapy in combination with behavioural interventions [3, 4]. General practitioners (GPs) play an important role in smoking cessation promotion by offering advice, treatment and support to their patients. In Switzerland, 60% of smokers expect their doctor to talk about smoking during consultations and 51% desire advice to help them quit smoking [5].

Nonetheless, doctors are less likely to prescribe medication for smoking cessation than for other cardiovascular risk factors [2, 3]. This may be due to a lack of confidence and knowledge in how to prescribe smoking cessation treatments. Doctors lack time and may also consider that discussing smoking cessation is intrusive, that the decision to smoke lies within the private sphere [5–7]. Most smokers attempt to stop smoking without requesting help, partly because of misconceptions regarding the efficacy and potential adverse effects of pharmacotherapies [8].

These barriers are exacerbated by the fact that smokers must “opt-in” to smoking cessation treatment. The current strategy, taught in Switzerland and in most countries, says that quitting advice must be adapted to each patient’s level of motivation to quit smoking using the 5 As model (combining information as well as relational and behavioural techniques). Guidelines recommend that health-care providers first ask patients if they are “ready” to quit, and only offer treatment to those who are ready and desire treatment [9]. This approach limits the reach of tobacco cessation management. Over two-third of Swiss smokers want to quit. However, only a small fraction wish to do so within the next month or two [10]. Hence, most smokers will not be prescribed smoking cessation medications or get behavioural support [9, 11]. Further, clinical trials have shown that smokers who report they are not planning a quit attempt actually quit at similar rates as those who are planning to quit, if they are provided support [9, 12]. Thus, all smokers should be offered treatment using an “opt-out” strategy.

This “opt-in” smoking cessation strategy is in contrast to the treatment of other common chronic medical conditions, such as hypertension and diabetes, where medical treatment is the default option [9, 13]. Accordingly, doctors should offer evidence-based care to all tobacco users without screening for readiness [6]. A before-after study in the UK tested new guidelines advocating “opt-out” quit smoking referrals for pregnant smokers [14]. The default referral approach doubled the number of pregnant smokers setting quit dates and reporting smoking cessation. A before-after study from Switzerland compared intensive cessation visits using motivational interviewing as a default choice for all hospitalized smokers with an acute coronary syndrome [15]. The proactive strategy increased the uptake of smoking cessation counselling and resulted in a non-statistically significant increase in smoking abstinence at 12 months (43% to 51%, *p* = 0.08) [15].

Another means of facilitating the prescription of smoking cessation medications is to use shared decision making (SDM). SDM is an ethical mean of offering quit aids to all current smokers without constraining their autonomy. To achieve SDM, clinicians and patients work together to understand the patient’s condition and determine how best to treat it [16]. SDM is particularly relevant in smoking cessation because medications such as nicotine replacement therapy (NRT), bupropion and varenicline have comparable efficacy but different harms and benefits due to their mechanism of action. A systematic review suggests that DAs may be effective in increasing smoking cessation knowledge, decision quality, and the number of quit attempts [17]. Our research group developed a DA for presenting available pharmacologic interventions for smoking cessation, available in both paper and electronic, online formats. The tool contains information for each treatment option about cost, possible adverse effects. The electronic version also has short animations showing how to use each treatment. The DA was designed to be accessible, intuitive and easy to use. During the consultation, this tool will support GPs in prescribing and help patients chose a pharmacological treatment [18].

The proposed study will therefore test the efficacy of implementing an “opt-out” strategy for smoking cessation treatment using a DA, for current smokers seen in primary care. We will train GPs to offer smoking cessation treatments as the default choice while using shared decision making with an encounter DA (electronic or paper version) to explicitly offer a choice of quit aids. This innovative approach has not been tested in the past and has the potential to increase the number of current smokers seen in primary care who make a quit attempt with a proven quit aid, thereby increasing the number of patients who quit smoking.

### Objectives

The primary objective is to evaluate the effect of a training program encouraging GPs to offer smoking cessation treatment as a default choice to all current smokers using an interactive, encounter decision aid (electronic or paper version), on the proportion of current smokers seen in primary care who have quit smoking 6 months after a baseline visit to their GP, as compared to enhanced usual care.

Secondary objectives are to: 1) evaluate the effect of the intervention on the proportion of patients who make quit attempts; 2) evaluate the effect of the intervention on the proportion of patients who use a quit aid; 3) evaluate the effect of the intervention on patients’ perceived involvement in discussions about smoking cessation; and finally, 4) measure the uptake of key behaviours, notably offering quit aids to all current smokers and use of the DA, by GPs.

## Methods and design

The trial protocol follows the SPIRIT guidelines (Appendix 1) and CONSORT statement for cluster randomized trials.

### Study design and setting

We will perform a cluster-randomized controlled superiority trial with block randomization at the GP level in private practices. GPs will be blinded to the arm allocation. This study is a clinical trial in the category A entailing minimal risks and burdens for participants. The study will be conducted in private practices the French language part of Switzerland.

### Participants and eligibility criteria

We will include a convenience sample of consenting GPs practicing in French-speaking Switzerland. We are focusing on French-speaking Switzerland to facilitate the development of training materials and the decision aid, and to avoid heterogeneity between GPs in French and German-speaking parts of Switzerland regarding their approach to smoking cessation. We aim to be inclusive of GPs at all levels of experience, all practice types, and baseline smoking cessation practices. GPs will recruit current daily smokers seen during routine visits at their practice.GP-level inclusion criteria:Private practices located in the Cantons of Vaud, Geneva, Neuchâtel, Jura, Fribourg or ValaisPractices with more than 80 individual patients seen in a typical monthWilling to recruit approximately twenty smoking patients within a target of six months of the training sessionGP-level exclusion criteria:Having completed a half-day or more of training on smoking cessation within the last 2 yearsHave plans to retire or relocate outside of French-speaking Switzerland in less than 12 monthsPatient-level inclusion criteria:Consider the GP as their primary care doctorUses tobacco daily (cigarettes, cigars, smokeless tobacco)At least 18 years of age at the time of inclusionPatient-level exclusion criteria:Consulting for an urgent complaint that precludes even a brief discussion of smoking cessationInability to follow the procedures of the study, e.g. unable to read French-language consent materials, severe psychiatric disorders and dementia.Previous enrolment in a smoking cessation trial within 1 yearCurrent daily use of a pharmacologic smoking cessation aid

### Sample size and power calculation

Based on previous research, we expect approximately 4% of current smokers seen with usual care conditions will report having quit smoking at 6 months after a baseline visit (32). This is based on a model whereby 20% of current smokers discuss a quit attempt (higher than usual with Hawthorne effect) (11), 10% get a specific pharmacologic aid or e-cigarette, and 4% successfully quit. We anticipate a 100% increase in the number of quit discussions in the intervention arm, so about 40% of current smokers discuss a quit attempt. Subsequently, 20% will use a pharmacologic aid or e-cigarette, and 10.5% will successfully quit. For the primary outcome will use mixed effect models accounting for clustered, repeated measures; without adjusting for baseline patient characteristics, we will compare two proportions, using a two-sided test for significance, β = 0.80, α = 0.05, and an intraclass correlation coefficient of 0.03. With these parameters, we need 20 clusters (i.e. individual GPs) in each arm, each with 20 current smokers who consent to inclusion. Assuming 15% drop-out or under-recruitment by individual GPs, we will aim to recruit 46 GPs with 23 patients each, so 1,058 patients. Individual GPs will be capped at 25 patients. No specific interim or safety analyses are planned. STATA version 16.0 for Windows (StataCorp LLC, College Station, USA) will be used for all statistical analyses. Stopping rules for the study: Recruitment of GPs will end when 46 have signed a contract to complete the training program and undergone randomization. Patient recruitment will end when all participating GPs have included ≥ 20 patients and 1,060 patients have been recruited overall. GPs will be considered inactive if they have not recruited patients within the last 6 months. The trial will also end if GP recruitment has ceased and all GPs have completed recruitment. If recruitment is too low (< 200 patient participants 12 months after beginning GP training programs), new recruitment strategies will be put in place and the study may be terminated.

We will conduct semi-structured interviews with a purposive subsample of patients and GPs to better grasp qualitative aspects of their experience with quit aids offered as a default choice and the electronic decision aids. We will aim to recruit a purposive sample of six GPs and ten patients in the intervention and control groups, respectively, or until data saturation. According to Guest et al., a sample of six to twelve participants per group is sufficient to reach thematic data saturation in qualitative interviews [19]. We will thus be guided by this principle but will also check for thematic data saturation before stopping the recruitment of new participants.

### Participant’s timeline

Recruitment of GPs will end when 46 have signed a contract to complete the training program and undergone randomization. Each GP will start the patient recruitment immediately after the training program during approximately the subsequent 6 months. Patient recruitment will end when all participating GPs have included ≥ 20 patients and 1,060 patients have been recruited overall. Patients will be followed during 6 months and GPs during 12 months.

### Randomization

The unit of randomization will be GPs who consent to participate in a smoking cessation training program and subsequently recruit eligible patients. The clinical trial protocol follows the CONSORT diagram in Fig. 1. Randomization, done by the study statistician, will be by blocks of two or four GPs to ensure balance between training dates. GPs from the same practice will be randomized together.

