### Controlling for contamination and other potential biases

Because this is a pragmatic study, there is a risk of co-administration of interventions and contamination between groups. We will be careful not to reinforce messages about default choices and SDM when contacting GPs about participant inclusion. While cluster-randomized controlled trials limit contamination between groups and better mirror routine clinical practice, they present special challenges not seen in traditional randomized controlled trials [20]. Because the unit of randomization is individual GPs but the unit of analysis is individual patients, there can be imbalances in patient-level confounders. Some clustering is addressed by using the intra-cluster correlation coefficient at the time of analysis. However, bias can come from the post-randomisation recruitment of patients. This bias is addressed by streamlining patient questionnaires, limiting post-randomisation selection bias, and reporting outcomes at both the cluster and individual level [21]. Under-recruitment by certain GPs can exacerbate imbalances, so a study coordinator blinded to treatment assignment will contact participating GPs within two weeks of the training and regularly thereafter to ensure that the inclusion process is functioning at their site.

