### Statistical methods

Data will be summarized for all patients and by group: intervention vs enhanced usual care. Continuous and count variables will be summarized as mean (95% confidence interval) or median (IQR) and categorical variables as numbers (percent). Binary outcomes at 6 months will be compared between the two arms intervention vs control using a logistic regression model with clustered-robust standard error estimates. To take into account the clustered repeated measurement design in testing the intervention effect and changes over time, repeated measurement outcomes will be analysed using a mixed-effect models. Depending on the distribution of the outcomes, a logistic regression model will be used for binary outcomes while count regression models (Poisson, negative binomial or zero-inflated negative binomial model) will be used for count outcomes. The intervention x time and others potential interactions will be tested in the models. In addition, subgroup analyses (sex, age, …) will be performed to assess in which subgroup the intervention is most effective. Data analysis will be performed using Stata 16 Software (StataCorp. 2019. Stata Statistical Software: Release 16. College Station, Texas: StataCorp LLC) and performed by a senior Biostatistician.

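### Colleagues from one practice are allocated together, yet the unit of randomisation and the power calculation are defined on individual GPs with no practice level

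*Protocol article*

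**What the plan says.** The Randomization section of the protocol article calls the GP the unit of randomisation and uses block sizes of 2 and 4 GPs. It then adds that "GPs from the same practice will be randomized together". The section on contamination and other biases repeats the GP as the unit: "Because the unit of randomization is individual GPs but the unit of analysis is individual patients". The sample size section defines the clusters in the same way: "we need 20 clusters (i.e. individual GPs) in each arm", each with 20 patients. It contains no number of practices, no number of GPs per practice and no practice-level correlation.

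For binary outcomes at 6 months, the Statistical methods section plans "a logistic regression model with clustered-robust standard error estimates". It does not name the clustering variable. No section limits enrolment to one GP per practice, and the joint-allocation rule itself expects shared practices.

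**The concern.** These statements cannot all hold once a practice contributes more than one GP. GPs who must go to the same arm are not independently randomised. Their patients may also share staff, catchment and local habits around smoking cessation. Two things are then at stake:

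- **Power.** The calculation credits the trial with more independent units than the allocation delivers.
- **Type I error.** Standard errors clustered on GP would omit the correlation between GPs of one practice, so the primary test would reject too often and its confidence interval would be too narrow.

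A lesser consequence is that blocks counted in GPs cannot always stay balanced when colleagues must share an arm. Two colleagues in a block of 2, for example, put the whole block in one arm.

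**Working it through.** **Inputs from the sample size section.** The control rate is 4% ("we expect approximately 4% of current smokers seen with usual care conditions will report having quit smoking at 6 months") and the intervention rate 10.5% ("20% will use a pharmacologic aid or e-cigarette, and 10.5% will successfully quit"). The test settings are "using a two-sided test for significance, β = 0.80, α = 0.05, and an intraclass correlation coefficient of 0.03", where the 0.80 is the power, as the abstract makes clear. There are 20 GPs of 20 patients per arm, with a recruitment target of 46 GPs of 23 patients.

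**Inputs assumed, because the documents give none.** g is the number of participating GPs per practice. ρp is the correlation between patients of different GPs in one practice, taken as 0.01 to 0.03. The upper end means that GPs within a practice do not differ at all.

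**Reproducing the plan.** With mean rate 0.0725, A = √(2 × 0.0725 × 0.9275) = 0.3667 and B = √(0.04 × 0.96 + 0.105 × 0.895) = 0.3638.

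- Without clustering, n per arm = [(1.96A + 0.8416B)/0.065]² = 248.7, so 249.
- Design effect = 1 + 19 × 0.03 = 1.57.
- 249 × 1.57 = 391 patients per arm, and 391/20 = 19.5, so 20 GPs per arm. This matches.
- Power at 400 per arm = Φ[(0.065√(400/1.57) − 1.96A)/B] = 81.0%.

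The match requires every GP to be an independently randomised cluster.

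**Adding the practice.** With m patients per GP, the design effect is 1 + (m − 1) × 0.03 + m(g − 1)ρp. At m = 20:

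| g | ρp | Design effect | Power, 20 × 20 per arm |
|---|---|---|---|
| 1 | any | 1.57 | 81.0% |
| 1.5 | 0.01 | 1.67 | 78.5% |
| 1.5 | 0.03 | 1.87 | 73.8% |
| 2 | 0.01 | 1.77 | 76.1% |
| 2 | 0.02 | 1.97 | 71.6% |
| 2 | 0.03 | 2.17 | 67.4% |

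At g = 2, 80% power needs 249 × 1.77/20 = 22.04 to 249 × 2.17/20 = 27.02 GPs per arm, so 23 to 28 instead of 20.

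If practices differ in size, g is the average counted per patient. An equal mix of one-GP and two-GP practices gives g = (1 × 1 + 2 × 2)/3 = 1.67, between the rows for 1.5 and 2.

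**Full target, 23 × 23 = 529 per arm, no loss.** At g = 1 the design effect is 1 + 22 × 0.03 = 1.66 and power is 88.8%. At g = 2 the design effect is 1.89, 2.12 or 2.35, and power is 84.5%, 80.1% or 76.0% (ρp 0.01, 0.02, 0.03).

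**Type I error if standard errors are clustered on GP.** At g = 2 the true standard error is larger by √(1.77/1.57) = 1.06 to √(2.17/1.57) = 1.18. The actual two-sided error is 2[1 − Φ(1.96/ratio)], about 6.5% to 9.5%.

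**Simulation check.** The null was simulated with 10 practices × 2 GPs × 20 patients per arm, a 5% quit rate, a total correlation of 0.03 and 20,000 runs. The GP-clustered z-test rejected in 8.6% to 8.8% of runs with half the correlation shared across the practice, and in 11.1% to 11.3% with all of it shared. With none shared it still rejected in 6.0% to 6.4%, which is few-cluster bias and not the practice effect. Clustering on practice with t critical values gave 5.7% to 5.9%.

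**The case against.** The strongest reply is that every consequence is conditional. Power falls only if some practices supply two or more GPs and outcomes correlate across those GPs, and the documents quantify neither. The intervention trains individual GPs, so much of the correlation may sit with the GP and not the practice. The standard-error problem also needs the analysis to cluster on GP, which Statistical methods does not say. Choosing the clustering variable can properly be left to an analysis plan, and clustering on practice would remove that part of the concern. Finally, the 46 × 23 target exceeds the 20 × 20 per arm used in the calculation, and patients lost to follow-up stay in the primary analysis as continuing smokers.

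Most of this stands as a limit on size. A reader might infer that the standard errors are too small and the 80% power overstated as a matter of fact. The documents do not support that, because GP-level clustering is only the natural reading of the sample size and bias sections, and single-GP practices would leave everything unchanged. Nor should the simulated 8.6% to 11.3% be put down wholly to ignoring practice, since roughly 1 point or more is few-cluster bias of the z-test.

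The recruitment margin helps but is not free, because the article already assigns it to 15% drop-out or under-recruitment. What the reply does not remove is the contradiction over the unit of randomisation and the cluster count built on it.

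**Conclusion.** The inconsistency is real and should be fixed. The joint-allocation rule makes the practice the randomised unit wherever GPs share one, while the stated unit and the power calculation treat every GP as independent. The stated 80% is right if each practice supplies one GP, or if outcomes do not correlate between GPs of a practice (apart from lost degrees of freedom).

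Otherwise the loss runs from negligible to material: a few points at 1.5 GPs per practice and low correlation, and about 14 points (81.0% to 67.4%) at two GPs in every practice and the highest correlation assumed. The type I error inflation holds only if the analysis clusters on GP. All these ranges rest on assumed values of g and ρp.

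**What to change.** - Reconcile the Randomization, sample size and bias sections by naming the practice as the unit of randomisation, with a single-GP practice as a cluster of one GP. Form the blocks on practices.
- State that the cluster-robust standard errors are computed on practice, or nest GP within practice in the mixed models. Use t critical values on (number of practices − 2) degrees of freedom.
- Restate power as a range over GPs per practice and between-GP correlation, at both 20 × 20 per arm and the full target, and replace the assumed g with the actual number once it is known.

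The cost is a change of clustering variable, a wording amendment, a slightly wider confidence interval and a slightly lower stated power. The t reference lowers power a little further: at 20 × 20 per arm it gives 79.4% at one GP per practice (38 df) and 71.9% to 63.1% at two (18 df). If all practices turn out to have one GP, the change of cluster level alters nothing.
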